### Intervention

Apart from the trial airway management method (LMA or ETI), other clinical decisions will be made by the practitioners at each site according to their clinical judgement and hospital protocol, including anesthesia induction, maintenance and recording, anesthetic drug use and dosage, surgical approach, and ICU treatment.

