### Primary outcomes

The primary outcomes are the incidence of PPCs (diagnostic criteria shown in Tables 3 and 4) and perioperative mortality rate.

**Table 3 Tab3:** Classifications of PPCs

Grading	Definition
0	No pulmonary complications
1	Any one of the following: cough, minor lung atelectasis (no obvious cause), dyspnea (no obvious cause)
2	Cough and sputum production (no obvious cause), bronchospasm (new-onset asthma or exacerbation of existing asthma that requires treatment), hypoxemia (SpO2 < 90% or PaO2 < 60 mmHg while breathing air), atelectasis (diagnosed by radiography or abnormal pulmonary sign with T > 37.5), hypercapnia (temporary or requires treatment; caused by medication or over-ventilation)
3	Pleural effusion (that requires drainage), suspected pneumonia (indicated by radiography, with or without microbiologic findings), diagnosed pneumonia (diagnosed based on the combination of radiology finding and microbiology evidence such as Gram staining or culture), pneumothorax (suggested by X-ray: observation of a lucent gas space devoid of pulmonary vessels between visceral pleura and the parietal pleura or symptoms of dyspnea, chest pain, irritating cough), noninvasive or invasive mechanical ventilation < 48 h
4	Respiratory failure (that requires noninvasive or invasive mechanical ventilation for > 48 h)

*PaO2* partial pressure of oxygen, *SpO2* blood oxygen saturation, *T* body temperature

**Table 4 Tab4:** Definition of PPCs

Complications	Diagnostic criteria
Pneumonia	X-ray finding of a new or progressive pulmonary infiltration and meeting 2 of the following 3 indications:
	(1) Cough, exacerbation of dyspnea or purulent sputum
	(2) Body temperature above 38 °C or under 36 °C
	(3) WBC > 12,000 or < 4000/μL
Atelectasis	Mainly based on X-ray findings as follows:
	Lung collapse
	Compensatory hyperinflation of adjacent ipsilateral lung tissue
	Wedge- or linear-shaped opacities
	Shifting of mediastinum
	Diaphragm move towards the collapse
Pleural effusion	X-ray finding of obscure or disappearance of costophrenic angle, obscured ipsilateral diaphragm
SIRS	(1) Core body temperature > 38 °C or < 36 °C
	(2) HR > 90 bpm, in cases of atrial arrhythmia, ventricular rate > 90 bpm; exclude when used medications that may affect heart rate
	(3) RR > 20 bpm, or PaCO2 < 32 mmHg (4.2 kPa), or urgent mechanical ventilation used
	(4) WBC > 12,000 or < 4000/μL

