Sepsis	(1) Positive microbiologic culture from blood, or definite tissue infection, presence of abscess
	(2) Meets at least 2 SIRS definitions
ALI/ARDS	(1) Lung injury of acute onset (within 1 week or progressive)
	(2) Hypoxemia, PaO2/FiO2 ≤ 300/200 mmHg
	(3) X-ray showing obscured bilateral lobes which cannot be explained by effusion, atelectasis, or nodules
	(4) Respiratory failure that cannot be explained by heart failure or hypervolemia

*PaO2* partial pressure of oxygen, *FiO2* fractional inspired oxygen concentration, *HR* heart rate, *RR* respiratory rate, *WBC* white blood cell, *SIRS* systemic inflammatory response syndrome, *ALI* acute lung injury, *ARDS* acute respiratory distress syndrome

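### Table 3's grade 2 hypercapnia criterion names a cause that lowers PaCO2, and its hypoxemia criterion leaves patients on oxygen without a clear scoring rule

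*Protocol article*

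**What the plan says.** The Primary outcomes section states: "The primary outcomes are the incidence of PPCs (diagnostic criteria shown in Tables 3 and 4) and perioperative mortality rate". Table 3 grades complications from 0 ("No pulmonary complications") to 4. Two of its grade 2 items concern gas exchange:

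- "hypercapnia (temporary or requires treatment; caused by medication or over-ventilation"
- "hypoxemia (SpO2 < 90% or PaO2 < 60 mmHg while breathing air"

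Table 4 has no separate entry for hypercapnia or hypoxemia. It uses an oxygen-adjusted measure once, inside the ALI/ARDS definition: "Hypoxemia, PaO2/FiO2 ≤ 300/200 mmHg". That line stands beside acute onset, bilateral X-ray change and otherwise unexplained respiratory failure. The only PaCO2 figure in either table is a low one, below 32 mmHg, under SIRS.

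Under Data collection and follow-up, a blood gas analysis is taken at baseline, and PPC level and blood gases are evaluated on days 1, 3 and 7 and before discharge. Caregivers and patients are not blinded, while data collectors are (Blinding, randomization, and allocation concealment). Apart from the airway device, "other clinical decisions will be made by the practitioners at each site according to their clinical judgement and hospital protocol" (Intervention).

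**The concern.** These items help define a primary outcome, so each must be one that an assessor can apply. The hypercapnia item contains a cause that runs the wrong way. An assessor at one of the 17 centers must apply it literally, and so exclude non-drug hypercapnia, or guess what was meant. Different guesses mean different scoring of the same patient. COPD patients are expected, since Table 2 gives COPD a risk point, so CO2 retention from a pulmonary cause is a realistic event here.

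The hypoxemia item raises a related problem. Oxygen is given by carers who know the device. If their oxygen practice differed by arm, the counted hypoxemia could differ with no difference in lung function. Blinded assessment does not remove this, because the masking happens before the assessor sees the value.

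**Working it through.** The plan gives no event rate for hypercapnia or hypoxemia, so there is no figure of its own to reproduce. The check is mainly a reading of the two tables.

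**Step 1: hypercapnia.** Hypercapnia is a raised PaCO2. Over-ventilation clears more CO2 and lowers PaCO2. Of the two causes named, over-ventilation can therefore yield no events, which leaves medication. Hypoventilation, obstruction and COPD exacerbation are not named.

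**Step 2: what else could make such a patient an event.**
- Grade 1: "Any one of the following: cough, minor lung atelectasis (no obvious cause), dyspnea (no obvious cause"
- Grade 2: cough with sputum, bronchospasm, atelectasis
- Grade 3: "noninvasive or invasive mechanical ventilation < 48 h"
- Grade 4: respiratory failure ventilated for more than 48 h
- Table 4: ALI/ARDS

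If any grade above 0 counts as a PPC, non-drug hypercapnia is lost only when none of these applies, and is under-graded when only a grade 1 sign applies.

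**Step 3: hypoxemia under both readings.** Reading A applies the room-air condition to SpO2 and PaO2. Reading B applies it to PaO2 only.

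| Patient | Reading A | Reading B |
|---|---|---|
| PaO2 59 mmHg on air | met | met |
| SpO2 below 90% on oxygen | not met | met |
| PaO2 70 mmHg on FiO2 0.40, SpO2 at or above 90% | not met | not met |

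The values in rows 1 and 3 are illustrative. The second row shows that the two readings score one patient differently. In the third row, PaO2/FiO2 = 70/0.40 = 175 mmHg, below both Table 4 limits (300 and 200), yet the grade 2 item is not met under either reading.

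**Step 4: would Table 4's limit of 300 serve as the on-oxygen rule?** Air has FiO2 0.21. The room-air limit therefore corresponds to PaO2/FiO2 = 60/0.21 = 286 mmHg. Take a ratio of about 290:
- On air: PaO2 = 0.21 × 290 = 61 mmHg, not an event.
- On FiO2 0.40: PaO2 = 0.40 × 290 = 116 mmHg, an event under a limit of 300.

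Giving oxygen would then create events, so scoring would still depend on oxygen use, in the opposite direction.

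**Step 5: power.** Inputs from Sample size estimations: 15% versus 10%, α = 0.05 (two-sided), and 3000 per group less 10% = 2700. The share of events lost is an assumption, equal in both arms, from 0 to 30%.

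Power = Φ{[|p1 − p2|√n − 1.96√(2p̄(1 − p̄))] / √[p1(1 − p1) + p2(1 − p2)]}

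- No loss: [0.05 × 51.96 − 1.96 × 0.4677] / 0.4664 = 3.61, power 99.98%.
- 30% loss (10.5% versus 7.0%): [0.035 × 51.96 − 1.96 × 0.3996] / 0.3988 = 2.60, power 99.5%.

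The issue is therefore endpoint validity and possible differential ascertainment.

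**The case against.** The strongest reply is that this is a wording slip in one sub-item of a broad composite. The author may have meant the opposite of over-ventilation, or the causes may be examples only. That may be so, but the text fixes a rule for a primary outcome and the rule is wrong as it stands.

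A second reply is that a condensed article may leave the PaCO2 limit, and any rule for patients on oxygen, to the full protocol. This stands: their absence is not charged as an error. What remains is the reversed cause and a room-air condition that can be read in two ways, both in the text shown. Room-air thresholds are in themselves a coherent definition.

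A reader might infer that real failures of gas exchange are scored as no event. The documents do not support that. Any ventilation reaches grade 3 or 4, symptoms and radiographic signs give grades 1 and 2, and ALI/ARDS has its own route. Nor is it settled that hypoxemia can be met only on room air, since under Reading B a low SpO2 on oxygen counts.

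A reader might also try to size the bias. With 6% true hypoxemia in both arms, and 30% (ETI) and 20% (LMA) of those patients on oxygen when sampled, the counted rates are 6% × 0.70 = 4.2% and 6% × 0.80 = 4.8%. At 50% and 20% they are 3.0% and 4.8%. None of these inputs is in the documents, and nothing there says that oxygen use differs by device. The sum also treats every masked case as a lost primary event, although step 2 of the working lists other routes and assessment is repeated. In this example the bias would hide an LMA benefit rather than create one.

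**Conclusion.** The hypercapnia criterion is wrong as written and should be corrected. Its literal effect is to admit only drug-related hypercapnia; other CO2 retention is missed when isolated and under-graded when accompanied only by a grade 1 sign. This assumes that any grade above 0 counts as a PPC, which Table 3 implies through its grade 0. If a higher grade were the threshold, the under-graded cases would be lost as well.

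The hypoxemia point is secondary and holds in part. The scope of the room-air condition is ambiguous, and oxygen can mask hypoxemia under either reading. The size and direction of any bias between arms cannot be derived from the documents. Power is not affected in any way that matters.

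**What to change.** 1. **Hypercapnia.** Delete the cause clause, or correct the reversed cause. Score the item from the blood gases already scheduled on days 1, 3 and 7 and before discharge, against a stated PaCO2 limit not already exceeded on the baseline gas.
2. **Hypoxemia.** State whether the room-air condition covers SpO2, PaO2 or both. Add a scoring rule for patients on oxygen, reconciled with Table 4 and consistent with the room-air limit (a PaO2/FiO2 of about 286 mmHg). If another cut-off is chosen, justify it; 300 would let oxygen itself create events.
3. **Timing.** Trial status reports that recruitment is under way. Make the change blind to outcome by arm, document it as an amendment, and report a sensitivity analysis under the present Table 3 text.

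The change affects scoring only, not oxygen treatment. It costs a revision of Table 3 and the recording of FiO2 or oxygen flow with each gas. The downside is that FiO2 on nasal oxygen is an estimate, and it may not be recoverable for patients already enrolled, so the on-oxygen rule may be incomplete for them.

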Geriatric patients often have limited mouth opening and cervical movement, poor cardiovascular tolerance, and altered pharmacokinetics. Under these circumstances [5], a laryngeal mask airway (LMA) is considered a good alternative to endotracheal intubation (ETI) because of its advantageous characteristics such as ease of insertion [13], less irritation to the airway, less reliance on muscle relaxant, and better patient comfort [14]. As a supraglottic airway device, however, it does not separate the trachea from the esophagus; therefore, the LMA is associated with higher incidence of aspiration of gastric contents, especially in susceptible patients with a history of gastroesophageal reflux disease [15]. Moreover, the LMA is not recommended for use in lengthy surgery, morbidly obese patients, or certain other types of surgeries in which more control of the breathing (e.g., heart, lung, and brain surgeries) [16] is required. Therefore, the LMA and ETI both have major roles in daily anesthetic practice, and their influences on PPCs under various circumstances are inevitable topics for question.

In contrast to the popularity of LMA or ETI usage in geriatric surgeries, research evidence about their effect on PPCs is scarce and incomprehensive. Our group published a retrospective single-center study that compared LMA and ETI use in geriatric patients who underwent elective abdominal surgery, and we found that, among those who were transferred into the intensive care unit (ICU), the LMA group was associated with lower incidence of atelectasis and pulmonary embolism [17]. To better clarify whether the use of LMA is superior to ETI for elderly surgical patients and provide sufficient evidence for clinical decision-making, we have designed the current large-scale, randomized, controlled clinical trial. Its rationale, design, and protocol will be described in this paper.

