**Fig. 2 Fig2:**
[figure not shown]
Standard Protocol Items: Recommendations for Interventional Trials (SPIRIT) figure for the POLMA-EP trial

Upon arrival, a series of baseline information will be collected, including the patient’s demographics, cause of hospitalization, elective surgery type, medical history, anaphylactic history, and co-morbidities and concomitant medication. Physiological parameters will also be collected, including blood pressure (BP), heart rate (HR), respiratory rate (RR), core body temperature (or axillary temperature + 0.5), ASA classification level, and risk for PPCs. The patient’s cardiovascular, neurological, respiratory, endocrine, and urinary functions will be evaluated and recorded. Laboratory tests including routine blood test, blood gas analysis, and pulmonary function indicators such as vital capacity (VC), forced vital capacity (FVC), forced expiratory volume in 1 s (FEV1), and peak expiratory flow (PEF) will also be measured and documented.

On the day of surgery, anesthetic and surgical recording will also be completed. This will include anesthesia type and duration, mechanical ventilation length, surgery time, PACU stay, blood products (red blood cells/plasma/platelets/fresh frozen plasma/albumin) transfusion, fluid infusion (crystalloid solution and artificial colloids), amount of bleeding, intubation type, times of attempts, ventilation mode, positive end-expiratory pressure (PEEP), tidal volume, types and dosage of anesthetic drugs, and ICU admission and stay.

The PPC level, routine blood tests, blood biochemistry, and blood gas analysis of each patient are evaluated at days 1, 3, and 7 and before discharge. Before discharge, important examinations such as pulmonary radiography and sputum and blood cultures will be completed and recorded. For PPCs, treatments including medication (drug name and dose) and mechanical ventilation (mode, duration, and other parameters) will be documented. In cases of death, the time, cause, and relativity to surgery or anesthesia will be evaluated and recorded.

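### Table 3 lets grade 3 pneumothorax be met by symptoms instead of the X-ray sign, so the same symptoms can be graded 1 or 3 and some can enter the PPC count without imaging

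*Protocol article*

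**What the plan says.** The Primary outcomes section of the protocol article states: "The primary outcomes are the incidence of PPCs (diagnostic criteria shown in Tables 3 and 4) and perioperative mortality rate". The wording of these tables therefore decides who has a primary event.

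Table 3 puts pneumothorax in grade 3. The criterion opens with the film, "pneumothorax (suggested by X-ray: observation of a lucent gas space devoid of pulmonary vessels", and continues "between visceral pleura and the parietal pleura or symptoms of dyspnea, chest pain, irritating cough". Grade 1 of the same table reads "Any one of the following: cough, minor lung atelectasis (no obvious cause), dyspnea (no obvious cause". Table 4 has no pneumothorax row.

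Under Data collection and follow-up, the PPC level and blood tests "are evaluated at days 1, 3, and 7 and before discharge". On imaging, the section says: "Before discharge, important examinations such as pulmonary radiography and sputum and blood cultures will be completed and recorded". It does not make the film a condition for any grade. A PPC score is taken again at day 28 ± 7, and follow-up contacts are by telephone.

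**The concern.** A film cannot show symptoms, so the word *or* makes the symptom list a second route to the diagnosis that needs no imaging. Two of the three symptoms already have a place in grade 1. The third, chest pain, appears in no other row of Table 3.

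Two things are at stake. One is the grade: the same findings can be recorded two grades apart, and 17 centers can resolve this differently. The other is the primary incidence: some patients without a pulmonary finding can be counted as having a PPC. The criterion is also subjective, in a trial whose patients and caregivers are not blinded and whose Discussion admits a risk that assessors become unblinded.

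**Working it through.** **1. Is the symptom route a real alternative?** The documents give no figure to reproduce, so this is a comparison of the entries.

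- Grade 3 suspected pneumonia: "suspected pneumonia (indicated by radiography, with or without microbiologic findings". Imaging is required. Diagnosed pneumonia also needs a radiological finding.
- Grade 2 atelectasis: radiography, or an abnormal lung sign together with a temperature above 37.5. Here *or* does introduce a non-film route, but one with a clinical sign and a measured temperature.
- Grade 3 pneumothorax: the X-ray sign, or symptoms. The second route needs nothing objective, yet scores one grade above atelectasis.

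Nothing in Table 4 or elsewhere in the article overrides the pneumothorax wording.

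**2. What can each reading produce without the X-ray sign?**

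| Finding | Own row in Table 3 | If one symptom is enough | If all three are needed |
|---|---|---|---|
| Irritating cough alone | 1 | 1 or 3 | 1 |
| Unexplained dyspnea alone | 1 | 1 or 3 | 1 |
| Explained dyspnea alone | 0 | 0 or 3 | 0 |
| Chest pain alone | 0 | 0 or 3 | 0 |
| All three together | 1 (cough) | 1 or 3 | 1 or 3 |

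The last row holds on both readings, so the overlap between grades 1 and 3 does not depend on how the list is read. New events (0 becoming 3) arise only if one symptom is enough.

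The gap is widest where a film is least likely to exist: at the early visits, since the only radiography the text schedules is before discharge, and at the day 28 telephone score.

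**3. Effect on the primary incidence.** The article does not say which grade counts as a PPC, so both cases are shown.

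*Any grade of 1 or more counts.* Cough and unexplained dyspnea are already events. The loose rule adds only chest pain alone and explained dyspnea. Inputs: 15% (ETI) and 10% (LMA) from Sample size estimations; 3,000 per group less 10% attrition = 2,700 per arm. Assumption, not in the document: among patients with no other PPC finding, a share *c*, equal in both arms, has chest pain only and is scored as pneumothorax.

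ETI = 0.15 + 0.85*c*; LMA = 0.10 + 0.90*c*.

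- *c* = 0: 15.0% vs 10.0%, risk ratio 0.10/0.15 = 0.67
- *c* = 2%: 0.15 + 0.017 = 16.7% vs 0.10 + 0.018 = 11.8%, risk ratio 0.71
- *c* = 5%: 0.15 + 0.0425 = 19.25% vs 0.10 + 0.045 = 14.5%, risk ratio 0.75

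The difference shrinks from 5.0 to 4.9 and 4.75 percentage points. Power at 2,700 per arm (two-sided 0.05) stays at about 99.9% and 99.7%. If all three symptoms are needed, nothing is added to this incidence, because the cough already makes the patient grade 1.

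*A higher grade is the threshold.* Cough and dyspnea alone would no longer be events, so every symptom-only pneumothorax adds one. The same formula applies with a larger share *q*, if 15% vs 10% is taken as the contrast at that threshold (a further assumption):

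- *q* = 10%: 23.5% vs 19.0%, risk ratio 0.81, power 98.2%
- *q* = 20%: 32.0% vs 28.0%, risk ratio 0.875, power 89.4%

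**The case against.** The strongest counter-argument is that the list may describe the joint symptom picture of a suspected pneumothorax. Grade 1 says explicitly when a single symptom is enough; the pneumothorax entry does not. On that reading isolated cough stays grade 1, and isolated chest pain or explained dyspnea stays grade 0. This stands as a limit: the text permits an upgrade and does not force one. It does not rescue the wording, because all three symptoms with a clear film would still qualify and would still overlap grade 1.

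There are also partial safeguards: radiography before discharge, and data collection blinded to allocation. Both make it less likely that symptom-only labels persist or differ by arm. Neither makes the film a condition for the grade.

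A reader might go further. The Background credits the LMA with "less irritation to the airway", so the rule might seem to manufacture an excess of serious complications under ETI. The documents do not support that as a conclusion. They give no cough rate for either device, and the article plans no test of grade 3 or higher, so a false-positive rate for such a test would rest on invented inputs for an unplanned analysis. Nor does the table mention wound pain or call grade 3 severe: it says chest pain, and grade 3 on a scale from 0 to 4.

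**Conclusion.** The point holds as a faulty criterion in the primary outcome. Grade 3 pneumothorax can be met without the X-ray sign, the number of symptoms needed is not stated, and the entry overlaps grade 1.

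If any grade counts as a PPC, the harm is mainly to the grading, plus a modest dilution: risk ratio 0.67 to about 0.71–0.75, assuming that one symptom is enough and that 2–5% in each arm have chest pain alone. Power is hardly touched, so the harm is to validity and interpretation. If a higher grade is the threshold, the event count is inflated directly, by an amount the documents do not allow one to fix. A bias between devices through irritating cough is possible and unquantified. The wording should be corrected before analysis; it does not by itself threaten the trial's conclusion.

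**What to change.** Reword the grade 3 entry so that pneumothorax requires the imaging sign already described, on X-ray or other imaging already taken, with or without symptoms. State that symptoms without that sign are scored only under their own row: grade 1 for cough or unexplained dyspnea, nothing for chest pain alone. Apply the same rule to the day 28 telephone score, where a pneumothorax then counts only if imaging exists. Re-check records already coded as pneumothorax without imaging, blind to arm, and document the change with its date.

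The cost is a one-line change to Table 3 and the case report form instruction, plus the blinded re-check. Recruitment was ongoing at publication, and the change touches an outcome definition, not patient care. The downside is that a pneumothorax that was never imaged is not counted.

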### Secondary outcomes

Secondary outcomes include ease of intubation (number of intubation attempts, disturbance to the following gastric tube insertion), anesthetics consumption, treatment for PPCs, duration of surgery, anesthesia recovery time and performance, time of PPC onset, postanesthesia care unit (PACU) stay, ICU admission and stay, re-admission rate, in-hospital days, hospitalization cost, and patients’ satisfactory score.

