## Statistics and data analysis

### Sample size estimations

Power Analysis and Sample Size (PASS) software (version 11.0; Number Cruncher Statistical Software (NCSS), LLC, Kaysville, UT, USA) was used for the sample size calculation. The χ^2^ test for a multiple proportions procedure was used. With an α = 0.05, a power of 90%, an effect size = 0.09, and degrees of freedom = 2, we estimated that 2584 patients would be required for our study. If the attrition rate was set at 10%, a total of 6000 patients (3000 in each group) would be required. The effect size was calculated from the assumption that the LMA would cause a reduction from 15% to 10% for the incidence of PPCs. The incidence of PPCs for patients undergoing different types of surgeries has been reported to be in the range of 1–23% [5]. Therefore, a proportion of 10% of the patients in the LMA group were expected to develop PPCs, and this was used to calculate the sample size.

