### Statistical analysis

Statistical analyses will be performed by an independent statistician using SAS 9.4 software (SAS Institute Inc., Cary, NC, USA). After normality testing, the patients’ data will be presented as the mean and standard deviation (SD) if they are normally distributed; otherwise, they will be presented as the mean and interquartile range. To compare numerical data, a paired or an unpaired *t* test will be used for normally distributed data, and the Kruskal-Wallis test will be used for skewed data. The χ^2^ test and Fisher’s exact test will be used to compare proportional data. When two χ^2^ tests are performed, the *P* value is adjusted to 0.025. A *P* value < 0.05 will be considered statistically significant. If *P* < 0.05, the Nemenyi test will be used to compare the difference between two groups. A logistic regression model will be developed to detect any potential confounding factors.

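### Time of PPC onset exists only for patients who develop a PPC, so the tests stated for numerical data compare a subset formed after randomisation; ICU stay needs a one-line clarification

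*Protocol article*

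**What the plan says.** The Secondary outcomes section of the protocol article names "time of PPC onset, postanesthesia care unit (PACU) stay, ICU admission and stay" in a longer list. It does not say which patients contribute a value for onset or for ICU stay.

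The Statistical analysis section then sets one rule for all numerical data. A paired or unpaired t "test will be used for normally distributed data", and "the Kruskal-Wallis test will be used for skewed data". Proportions go to χ² or Fisher's exact test. The only model named is a logistic one: "A logistic regression model will be developed to detect any potential confounding factors". No time-to-event or cumulative-incidence method appears.

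The Sample size estimations section assumes that "the LMA would cause a reduction from 15% to 10% for the incidence of PPCs" and adds: "If the attrition rate was set at 10%, a total of 6000 patients (3000 in each group) would be required". PPC incidence and perioperative mortality are the primary outcomes. Under Data collection and follow-up, PPC level is assessed on days 1, 3 and 7 and before discharge, and a PPC score is taken again at day 28 ± 7.

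**The concern.** A t test or a rank test needs one number per patient. For time of PPC onset, a patient who never has a PPC has no number, and neither test can use a censored time. Following the text leaves only the cases.

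The cases are selected by an event after randomisation, and that event is itself a primary outcome that the trial expects the device to change. If LMA removes some kinds of PPC more than others, the cases left in the LMA arm differ in mix from those in the ETI arm. Preventing early events then looks like delayed onset; preventing late events looks like earlier onset. Neither describes what happened to any patient, and the protection given by randomisation is lost for this outcome.

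ICU stay raises a related but weaker question. Stay could be compared among the admitted only, which has the same defect, or as ICU days in everyone, which does not. The article does not say which is meant.

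**Working it through.** The article gives no figure for onset or ICU stay, so there is none to reproduce. The inputs taken from it are 15% vs 10%, 3,000 per arm and 10% attrition. The total sample size calculation is not relied on.

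**Who enters the onset comparison**

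- Analysed per arm: 3,000 × 0.90 = 2,700.
- ETI cases: 2,700 × 0.15 = 405. LMA cases: 2,700 × 0.10 = 270.
- Patients with no onset time: 85% (ETI) and 90% (LMA).

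**Size of the effect, early/late model (assumed)**

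The article gives no onset distribution. Assume early PPCs start on day 1 + Poisson(0.5), mean 1.5, and late PPCs on day 4 + Poisson(1.5), mean 5.5, in both arms. ETI has 10% early and 5% late; LMA has 10% in total, split in different ways. Mean onset among cases is (early rate × 1.5 + late rate × 5.5) / total rate.

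- ETI: (0.10 × 1.5 + 0.05 × 5.5) / 0.15 = 2.83 days.
- LMA with early 5%, late 5%: (0.075 + 0.275) / 0.10 = 3.5 days.
- LMA with early 8%, late 2%: (0.12 + 0.11) / 0.10 = 2.3 days.

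Share of 4,000 simulated trials with P < 0.05 among cases:

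| LMA early / late | Mean onset, ETI vs LMA (days) | Kruskal-Wallis | t test |
|---|---|---|---|
| 6.67% / 3.33% (prevention unrelated to timing) | 2.8 vs 2.8 | 5% | 5% |
| 7% / 3% | 2.8 vs 2.7 | 11% | 13% |
| 6% / 4% | 2.8 vs 3.1 | 32% | 34% |
| 8% / 2% (mainly late prevented) | 2.8 vs 2.3 | 87% | 93% |
| 5% / 5% (only early prevented) | 2.8 vs 3.5 | 97% | 98% |

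Repeat runs of the same model put the two mild cases at about 12% and at 32% to 35%. In the 8% / 2% row, LMA has fewer early PPCs (8% vs 10%) and fewer in total (10% vs 15%), yet the case-only test points to earlier onset.

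**Check on the visit grid (assumed)**

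Put ETI onsets at days 1, 3 and 7 in shares 50/30/20%: mean 0.5 × 1 + 0.3 × 3 + 0.2 × 7 = 2.8 days. Let 5 percentage points of PPCs be prevented, with a varying share of these on day 1. At 50%, equal to the share among all ETI onsets, the rank test rejects in 4.8% of trials. At 60, 70, 80 and 100%, LMA mean onset is 2.98, 3.16, 3.34 and 3.70 days, and rejection is 22, 66, 95 and 100%. The pattern does not hinge on the first model.

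**ICU stay (assumed)**

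Take 5% admitted under ETI, 70% of stays short (mean 1.5 days) and 30% long (mean 7), with LMA preventing 30% of admissions, all of them short.

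- Among the admitted: ETI 0.7 × 1.5 + 0.3 × 7 = 3.15 days; LMA (0.4 × 1.5 + 0.3 × 7) / 0.7 = 3.86 days.
- Per patient, zeros included: ETI 0.05 × 3.15 = 0.158; LMA 0.035 × 3.86 = 0.135.

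The direction reverses with the population, which is why it should be stated.

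**The case against.** The strongest reply is that no test is assigned to onset by name. The Statistical analysis section is a generic paragraph in a condensed article, and censoring rules and competing events usually belong in a statistical analysis plan. Part of this stands: the absence of such detail alone would be no finding. But the article does route numerical outcomes to two tests, and neither can take a patient without an onset time. That is a method fixed badly, not just a detail left out.

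Four stronger readings are tempting, and the documents do not support them.

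- **That a false result is to be expected.** Nothing in the article says that prevention depends on timing. Where it does not, the test keeps its 5% level.
- **That the simulated rejections are false positives under identical onset distributions.** Only the early and late components are identical. The mixture among cases truly differs between arms (67/33 in ETI against, say, 50/50 in LMA). The test detects that difference; the error lies in reading it as delay. A reader would also see PPC incidence beside it, which makes a reading of outright harm less likely.
- **That ICU stay has the same defect.** A non-admitted patient can be counted as 0 days, and Kruskal-Wallis then works in all randomised patients. With two equal arms of 2,700, each with 5% admitted, it rejected in 4.7% of simulated trials. Listing admission and stay as separate items suggests stay among the admitted, but does not settle it.
- **That exact onset dates are already recorded.** The article describes PPC level at set visits and mentions no onset date, although onset is a listed outcome.

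**Conclusion.** The point holds for time of PPC onset. As written, the comparison rests on about 405 against 270 cases, selected by a post-randomisation event that the trial expects the device to change. The chance of a misleading P < 0.05 runs from about 5% when prevention is unrelated to timing, through about 12% to 35% with mild imbalance, to about 97% when only early PPCs are prevented. The case counts follow from the article's own rates. The percentages rest on assumed onset distributions and show a range, not a forecast.

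For ICU stay the conclusion is only that the population should be stated. These are secondary outcomes, and neither the primary comparison nor the sample size is affected. The change should be made, but the trial does not depend on it.

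**What to change.** **Time of PPC onset.** Define it as time from surgery to first PPC in all randomised patients. Report cumulative incidence by arm with death before PPC as a competing event, and compare the arms with stratification by PPC risk score. Where no exact date is recorded, use a method that allows for onset known only to the assessment visit (days 1, 3 and 7, discharge, day 28), such as an interval-censored or discrete-time model. Give onset among cases as description, without a P value.

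**ICU stay.** State that ICU days are compared in all randomised patients, with 0 for those not admitted and a stated rule for deaths, because an early death shortens ICU days. Give stay among those admitted as description only.

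**Cost.** Analysis wording only, with no added patients or visits. PPC level by visit, ICU admission and stay, time of death and the risk score are already collected. Whether the case report form also holds an exact onset date should be checked before the method is fixed.
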